## 3. Results

### 3.1. Trial Progress

Ethical approval by the Medical Ethics Review Committee (MEC-U, Nieuwegein, The Netherlands) was received on 6 December 2021. Recruitment of participants started on 7 March 2022, in all participating centres. The trial has been registered at www.clinicaltrials.gov (accessed on 31 Octobre 2022) under registration number NCT05343403. Trial progress and information can also be found on www.zorgevaluatienederland.nl/neopartner (accessed on 28 August 2023). Currently, all 10 centres have started enrolling patients. Recruitment is expected to be completed by December 2023.

### 3.2. Reporting and Publication

The ultimate goal is to advocate for the development of a national guideline on FICare implementation in neonatal units across the Netherlands, thereby enhancing the quality of care and support provided to both infants and their families. The research findings will be reported according to the CONSORT 2010 guidelines for stepped-wedge cluster-randomised controlled trials [28]. These publications will provide detailed insights into the results reaching a wide audience of healthcare professionals and policymakers. Our research team will present the study’s findings at national and international conferences related to neonatology, paediatrics, and family-centred or integrated care. By presenting the study findings at conferences and meetings, we can target professionals directly involved in neonatal care and influence their practice. We will collaborate with relevant professional associations in neonatal care and paediatrics to share the study results. These associations include the Dutch Society of Paediatrics, Dutch Section of Neonatology, and other related organisations. To raise awareness among the general public about the benefits of FICare and its potential impact on neonatal care, we will initiate a public awareness campaign through social media and collaborations with relevant health-focused organisations. By adopting these dissemination strategies, we aim to ensure that the study’s results reach the various stakeholders, including parents, healthcare professionals, and policymakers.

## 4. Discussion

Although previous research has highlighted the importance of parental participation in neonatal care [16,24,25,26,74,75,76], the broad implementation of a care model in neonatal wards to achieve such collaboration with parents still lags behind [12]. In a survey with 400 parents held by our research group prior to this study, the FICare principles were, as reported by parents, hardly implemented in the Netherlands [77]. Moreover, although parental participation in medical rounds can play a crucial role in empowering parents [16], evidence of the best practice and effects of family-centred rounds on neonatal wards is missing. In an era of staff shortage where time seems to be perpetually scarce, a readily available blueprint to ameliorate parental participation on neonatal wards could help spread programs such as family-integrated care more easily. The implementation plan that is described in this study is tailored to the Dutch setting and developed in close collaboration with the neonatal parent and patient organisation (Care4Neo), putting parental involvement into practice from the very start. The protocol outlined in this manuscript provides an overview of a novel trial design to implement and sustain FICare in neonatal wards, while investigating the (expected beneficial) effects. Alongside the outcomes measured at the individual level (infants and parents), the outcomes measured at cluster level (healthcare professionals, adherence to the intervention, cost-effectiveness) could provide meaningful information for management in deciding on policy strategies.

By using the stepped-wedge cluster-randomised trial (swCRT) design, this study aims to deliver robust evidence on the effects of FCR as part of the FICare concept. Apart from the practical and ethical advantages the swCRT design offers for this particular intervention, the methodological and/or statistical approach also enlarges generalizability. For example, the design makes accounting for possible (substantial) confounding effects of factors such as hospital culture, policies, architecture and size possible. Also, with the awareness of the importance of parental involvement possibly also growing naturally in neonatal care practices, the interaction of time is considered in the analysis.

Up till now, the effect of FICare on the physiological stress response in both infants and parents, using biomarkers of stress, has remained unexplored. It is known that psychological distress in lactating mothers during lactation can alter the composition of human milk regarding macro- and micronutrients, as well as the hormonal and immunological components [78,79,80]. Human milk is considered to improve infant health outcomes by facilitating the transmission of nutrients, hormones and cytokines from mother to child. The stress response is regulated to a great extent by glucocorticoids and previous research has shown that psychosocial interventions can affect cortisol levels in human milk [81]. However, the effect of interventions targeted on parental participation on such biomarkers of stress has not been described thus far. Therefore, the analysis of the cortisol levels in both human milk, hair and buccal saliva that are included in this trial might reveal answers and substantiate the beneficial effects of FICare on reducing stress.

Another novel evaluation includes a broad spectrum of the cost-effectiveness of FICare, beyond the evaluation of the infant’s length of stay [76]. Although reducing length of stay might evidently reduce healthcare costs, the effect of FICare on length of stay differs between studies [74,76,82]. The socio-economic effects of FICare, such as timing of resuming work by parents or work absence of healthcare professionals, have not been evaluated yet. By describing the cost-effectiveness, this study could guide hospital management to support implementation of FICare on their neonatal wards.

Changing hospital care culture and professional working methods, as occurs with implementing FICare, might impact healthcare professionals. Qualitative research evaluating the experiences of healthcare professionals with the FICare concept reveals that nurses indeed experience an alteration in their (professional) role, shifting from a professional caregiver to more of a supporting and educational role [83]. While nurses describe their new role as enhancing the parent–staff relationship, the process itself of changing might create challenges [17]. The effect of such interventions on the overall work pleasure and engagement in work of healthcare professionals remains unknown.

An obvious limitation of this study is the non-blinding of participants (both parents and healthcare professionals) and researchers. The design of the study and the nature of the intervention makes for an unfeasible setting for blinding. However, the effects of the non-blinding design are expected to be very low on the patient (infant and parent) level, as researchers cannot influence the medical facts or responses given by parents. There is a possible bias introduced by not blinding healthcare professionals (as some could have been supporters of the FICare concept beforehand, influencing their judgement and responses to questionnaires), but this is also expected to be of low relevance. As the other outcomes on cluster level are all objective (such as cost-effectiveness), bias is not expected on this level.

Another point worth mentioning is the possible differences in the (quality of) execution of the intervention between hospitals. Many principles of both the FCR and the FICare rely on human factors such as the communicative and collaborative skills of the healthcare professionals. In an ideal setting, in the absence of any financial or time restrictions, a more extensive training, such as that described in Finnish studies, would be incorporated in the implementation strategy [75]. However, as it is clear that steps need to be made based on current practices and the possible positive effects of parental participation [12,25,26], we chose to work with an implementation strategy that is feasible for most hospitals regardless of size or staff shortage. The results of this trial might implicate the need for further improvement or extension of this strategy, for example, creating a “FICare-plus” strategy for high income countries’ level 2 wards, comparable to the work described by a Spanish research group [84] for level 3 settings and the work published in Canada on Alberta FICare [76].

Lastly, in this study, only participants that are willing and able to fill in the questionnaires in English or Dutch are included. We conclude this as a significant limitation of the study, as a total of 149 languages or dialects are spoken at home in the Netherlands, with more than 8 percent of the Dutch population speaking a different language than Dutch at home [85]. Unfortunately, due to the limited availability of the outcome measurement tools in languages other than Dutch or English, we were not able to overcome this limitation at this point in time. However, the FICare implementation will be accessible to all parents whose infant is admitted to the neonatal wards of the participating centres. It is our opinion that the goal of FICare should be to empower every parent according to their preferences, needs and abilities. As such, there is not one single form of FICare that suits every parent, but individual tailoring outside of the healthcare professional’s perspective or habits could form a challenge. Further research should thus focus on gaining more knowledge on what parents of all different cultures, socio-economic statuses and personal situations need in order to participate in the manner they prefer and are able to.

## 5. Conclusions

To our knowledge, the neoPARTNER study is the first stepped-wedge cluster-randomised controlled trial in level two neonatal wards to assess the impact of FICare with FCR on (longitudinal) parental mental health, neonatal health (including biomarkers of stress) and organisational outcomes. This will enable all stakeholders in neonatal care to gather relevant and useful data to optimise and further humanise neonatal care.

## Figures and Tables

**Figure 1 children-10-01482-f001:**
[figure not shown]
Visual overview of the study design. CP = control period; IMP = implementation period; IP = intervention period.

**Table 1 children-10-01482-t001:** Study procedures: parents and infants.

Timing	Subject	Outcome	Tool/Unit
Admission ^1^	Parents	Parental stress levels ^2^	PSS:NICU [31,32]
		Depression	PROMIS [50,51]
		Anxiety	PROMIS [50,51]
		PTSD	PCL-5 [45,46,48]
	Infant	Baseline characteristics	N/A
Discharge	Parents	Demographics	General questionnaire
		Parental stress levels	PSS:NICU [31,32]
		SDM	SDM-Q-9 [36,37]
		SDM preference	CPS [39]
		Depression	PROMIS [50,51]
		Anxiety	PROMIS [50,51]
		PTSD	PCL-5 [45,46,48]
	Mothers	Human milk biofactors	See text
	Infant	Breastfeeding rates	Index of breastfeeding [52,53]
		Length of stay	days
		Growth	Weight gain velocity [54]
		Glucocorticoid receptor methylation rate in buccal mucosal cells	Mquant method [55]
CA of 3 months of the infant	Parents	Follow-up characteristics	General questionnaire
		Depression	PROMIS [50,51]
		Anxiety	PROMIS [50,51]
		PTSD	PCL-5 [45,46,48]
		Hair cortisol	LC-MS/MS [56,57]
		Salivary cortisol	LC-MS/MS [56,57]
	Mothers	Human milk biofactors	See text
	Infant	Glucocorticoid receptor methylation rate in buccal mucosal cells	Mquant method [55]
		Salivary cortisol	LC-MS/MS [56,57]
CA of 6 months of the infant	Parents	Follow-up characteristics	General questionnaire
		Depression	PROMIS [50,51]
		Anxiety	PROMIS [50,51]
		PTSD	PCL-5 [45,46,48]
CA of 12 months of the infant	Infant	Neurodevelopment	ASQ [33,35]
		Medical costs	iMTA MCQ [58]
	Parents	Follow-up characteristics	General questionnaire
		Productivity costs	iMTA PCQ [59]
		Medical costs	iMTA MCQ [58]
		Depression	PROMIS [50,51]
		Anxiety	PROMIS [50,51]
		PTSD	PCL-5 [45,46,48]

SDM = shared decision-making; N/A = not applicable; CA = corrected age; PTSD = post-traumatic stress disorder. ^1^ Measurement at admission will only be performed in (parents of) infants born <35 weeks of gestation. ^2^ At admission, PSS:NICU questionnaire will only be sent to parents of infants who were born at an NICU.

**Table 2 children-10-01482-t002:** Study procedures: healthcare professionals and organisations.

Timing	Subject	Outcome	Tool/Unit
At start, halfway through and end of study	HCP	Demographics	General questionnaire
		Work engagement	UWES-9 [61]
		Autonomy	Subscale of JCQ [64]
		SDM	SDM-Q-Doc [37,60]
		Productivity costs	iMTA PCQ [59]
	Organisation	Work absence	Percentages of absenteeism
		Parental presence at rounds	No. of parents present, no. of rounds
		Duration of rounds	Minutes

HCP = healthcare professional; SDM = shared decision-making.

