### 2.2. Design

Due to the nature of the intervention, which involves changes to unit-level provision of care (medical rounds) and interaction between participants, there is a risk of cross-contamination. Therefore, to avoid contamination of patients and staff, the stepped-wedge cluster-randomised controlled trial design was selected. The trial is designed according to the CONSORT 2010 guidelines for stepped-wedge cluster-randomised controlled trials [28]. Randomisation will be performed using a random number generator, which will randomly assign the timing of start of intervention between sites. Hospitals will be stratified by level of care delivered (post-intensive care or not). The program will generate a series of blocks of varying sizes for each stratum and allocate units a time for intervention (3, 6, 9, 12 or 15 months, respectively) as is visualised in Figure 1.

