### 2.4. Study Population

In 2021, in the Netherlands, approximately 15% of (live) born infants were born preterm and/or small for gestational age, accounting for 25,018 infants [30]. According to Dutch policies, infants born with a gestational age < 32 weeks and/or birthweight < 1200 g or in need of intensive care (e.g., cardiorespiratory support) are born in/or treated at a NICU (level 3). In a Dutch level 2 neonatal ward, infants may receive non-invasive respiratory support, have central venous catheters and receive multiple medications. It is quite common for infants to be transferred between different hospitals prior to their final discharge to home.

In this paper, the intervention group will be referred to as the FICare-group and the control group as the standard neonatal care (SNC) group.

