### 2.8. Primary Outcome

The primary outcome of the study will be the level of parental stress at discharge. The Parental Stress Scale: Neonatal Intensive Care Unit (PSS:NICU) is the most widely used instrument to measure parental stress and stressors arising from hospitalisation of an infant on the NICU [31]. It measures the parental perception of stressors that are arising from the hospitalisation of their child, with a variety of health problems on any type of inpatient unit [32]. The design of this tool emphasises the 3 dimensions of the surroundings and experiences on an NICU: the environment of the unit (sights and sounds; 5 items), the appearance of the infant (14 items) and alterations in the parental role (7 items). The 3 subscales show an internal consistency (Cronbach’s α) of 0.73–0.94 [31,32]. A total of 26 items are scored from “not stressful at all” to “extremely stressful”, and both a subscore for each domain and a total score (ranging from 0 to 130) are given. Parents will be asked to fill out the PSS:NICU at discharge. The primary outcome will be defined as the mean difference in total PSS-NICU scores at discharge between the intervention and the control group.

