#### 2.10.2. Statistical Analysis

All analyses will be performed based on an intention-to-treat principle to minimise attrition bias. A sensitivity analysis with a per protocol analysis, including, for instance, only the infants and families who have not been transferred from the study site to another hospital before discharge home, will also be performed. Possible bias due to differential withdrawal or study drop-out will be assessed in this per protocol sensitivity analysis as well. We will consider performing a subgroup analysis based on clinical characteristics, to adjust for differences in (severity of) infants’ medical conditions.

Baseline characteristics of the intervention and control group will be compared using student *t*-tests for continuous normally distributed variables, and Chi-square tests for categorical variables. Non-parametric tests will be used for variables that do not follow a normal distribution. Missing data will be handled by multiple imputation chain equations (mice) [70] with adjustment for clustering [71]. Rubin’s rules will be applied to pool the results of the different imputed dataset [72]. As described and proposed by the Panel on Handling Missing Data in Clinical Trials, we will carry out sensitivity analyses with different missing data strategies adjusted for clustering [73]. We will consider missing completely at random, missing at random, and missing not at random approaches.

With a generalised linear mixed modelling (GLMM) analysis, we will analyse whether parental stress at discharge is decreased after the intervention. We will include the factor “cluster” (hospital) as random effects, and “step” will be included as fixed (time) effect. In a secondary analysis, adjustment can be applied for possible confounders, such as (medical) characteristics of the infant during hospital stay. Adjustment for possible time effects will be made.

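### The primary model leaves out NICU birth and the admission PSS:NICU score, which are already at hand for part of the sample; this costs some precision but causes no bias.

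*Protocol article*

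**What the plan says.** Section 2.8 sets the primary outcome: "The primary outcome will be defined as the mean difference in total PSS-NICU scores at discharge between the intervention and the control group". Section 2.10.2 describes the primary model as a generalised linear mixed model with hospital as a random effect, and step "will be included as fixed (time) effect". Adjustment for possible confounders may be applied in a secondary analysis, with infant characteristics during the stay as the example. A subgroup analysis on clinical characteristics will be considered.

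Table 1 lists the PSS:NICU at admission as well as at discharge. Footnote 1: "Measurement at admission will only be performed in (parents of) infants born <35 weeks of gestation". Footnote 2: "At admission, PSS:NICU questionnaire will only be sent to parents of infants who were born at an NICU". Read together, the admission score exists only for infants who were both born at an NICU and born before 35 weeks. To send the form, the trial must know which infants these are.

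NICU-born infants belong to the expected population. Section 2.4 describes level 3 care for "infants born with a gestational age < 32 weeks and/or birthweight < 1200 g or in need of intensive care" and adds: "It is quite common for infants to be transferred between different hospitals prior to their final discharge to home". Section 2.2 stratifies the randomisation of hospitals by whether they deliver post-intensive care.

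**The concern.** The trial collects an earlier measurement on its primary instrument from an identifiable group, and then states a primary model that uses neither the score nor membership of the group. With 600 families over 60 ward-quarters outside implementation (10 wards × 7 quarters, less one implementation quarter per ward), each cell holds about 10 families. Chance differences between cells in the number of NICU-born infants, and in how stressed their parents already were, add noise to the cell means from which the stepped-wedge contrast is built. A covariate that predicts the discharge score removes part of that noise without recruiting anyone. What is at stake is the width of the confidence interval and the power for the primary comparison.

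**Working it through.** **Inputs from section 2.10.1.** Difference 13 points = 0.5 SD, so SD = 13/0.5 = 26 and total variance = 676. ICC 0.01, so between-hospital variance τ² = 0.01 × 676 = 6.76 and residual variance σ² = 669.24. Eta = 0.5 × 13 = 6.5, read as the SD of a random treatment effect. Ten hospitals, two per step, seven quarters, one implementation quarter. 600 enrolled; with 25% missing, 600 × 0.75 = 450 analysed.

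**Assumptions of this check.** Two-sided alpha 0.05 (the article states none). The first sequence has one control quarter and each later sequence one more. The implementation quarter is excluded, leaving 60 cells. Cell sizes are equal: m = 450/60 = 7.5 or 600/60 = 10.

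**Formula.** For each hospital, V = (σ²/m)·I + τ²·J + η²·xx′, where x is the exposure indicator by quarter. X holds seven quarter effects and the treatment effect. The SE is the square root of the treatment element of (Σ X′V⁻¹X)⁻¹. Power = Φ(13/SE − 1.96).

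**The plan's own figure (80% power with 600).**
- 600 analysed, eta as SD 6.5: SE 4.61, power 80.6%.
- 450 analysed, eta as SD 6.5: SE 5.12, power 71.8%.
- 450 analysed, eta read as a variance of 6.5: SE 4.62, power 80.3%.
- 450 analysed, eta 0: SE 4.50, power 82.4%.

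The article does not fix the reading, so the 80% is neither confirmed nor called wrong. The present point does not depend on it.

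**Effect of using the admission score.** If a share p of families has the score and it correlates r with the discharge score, residual variance is multiplied by 1 − p·r². The article gives neither p nor r, so both are assumed over a range. With 450 analysed and eta as SD 6.5:

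| p | r | p·r² | SE | Power | Gain, points |
|---|---|---|---|---|---|
| none | – | 0 | 5.12 | 71.8% | – |
| 0.10 | 0.3 | 0.9% | 5.10 | 72.1% | under 1 |
| 0.10 | 0.5 | 2.5% | 5.07 | 72.7% | under 1 |
| 0.20 | 0.3 | 1.8% | 5.09 | 72.4% | under 1 |
| 0.20 | 0.5 | 5.0% | 5.02 | 73.5% | 2 |
| 0.35 | 0.6 | 12.6% | 4.87 | 76.1% | 4 |
| 0.50 | 0.7 | 24.5% | 4.62 | 80.4% | 9 |

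At p = 0.35 and r = 0.6, an unadjusted analysis would need about 515 families instead of 450 for the same SE.

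**Other readings, same extremes of p and r.** Eta 0, 450 analysed: 82.4% rises to between 82.7% and 90.6%. Eta as a variance of 6.5, 450 analysed: 80.3% rises to between 80.6% and 88.8%. Eta as SD 6.5, 600 analysed: 80.6% rises to between 80.8% and 87.6%. The starting power moves; the gain stays similar.

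**The case against.** **Nothing is contradicted or biased, and covariate lists often sit in a fuller document.** The first half stands. Every hospital contributes both conditions, hospital and step are in the model, and randomisation is stratified by post-intensive care. The second half stands only in part: the article names the terms of the primary model and assigns adjustment to an optional secondary analysis, which is a stated choice. A fuller plan could still adopt the score.

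**NICU birth could enter through the existing provisions.** The open-ended secondary adjustment, or the subgroup analysis under consideration, could take it in. True, but neither is committed to, and neither improves the primary estimate.

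**The gain rests on two unknown quantities.** This stands. The score needs NICU birth, birth before 35 weeks and a returned form. Infants treated at an NICU but not born there have none. If p is near 0.10 and r is moderate, the gain is under one point. The largest gain needs the top of both ranges.

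**Adjusting may remove part of the effect.** Wards are unblinded and their phase is already set when the form is completed, so a late form may reflect the intervention. This is a real caution for the score. It does not apply to the NICU-birth term, which is fixed before the ward stay.

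**Stronger readings that the article does not support.** A reader might infer from "It measures the parental perception of stressors that are arising from the hospitalisation of their child" that the discharge score carries stress from the level 3 stay, and that the effect is therefore diluted. This is plausible, but the period that parents are asked to rate at discharge is not shown. The admission form might equally be meant to capture the NICU stay, leaving discharge for the ward. The precision argument needs only a correlation between the two scores. A reader might also extend the point to the admission PROMIS and PCL-5. The article states no model for those outcomes, so their omission cannot be asserted.

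**Conclusion.** The point holds as a modest matter of efficiency. The primary model as stated omits NICU birth and an admission score that the trial already schedules for NICU-born infants under 35 weeks. The treatment effect is not biased by this. The cost is p·r² of residual variance: under 1 to about 9 percentage points of power over p = 0.10–0.50 and r = 0.3–0.7, with 450 analysed and eta as an SD of 6.5. These ranges are assumptions, and the baseline power depends on how eta and the missing-data allowance are read. The change is worthwhile because it needs no data beyond those planned, not because the present model is wrong.

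**What to change.** Before the data are analysed, add two terms to the primary model of section 2.10.2:

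1. an indicator for families of infants born at an NICU before 35 weeks, for whom the admission form was scheduled;
2. that indicator multiplied by the admission PSS:NICU total, centred within the group and set to 0 for families never sent the form.

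Impute admission scores only where a form was sent but not usable, never for families outside the group. Fix a completion window in advance and treat forms completed later as missing. Keep the model without these terms as a sensitivity analysis. If exposure before completion cannot be ruled out, the indicator alone can go into the primary model and the score into a named sensitivity analysis. It would also help to state which period parents are asked to rate at discharge.

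The cost is wording in the analysis plan, two more parameters and a check of completion dates. Recruitment began on 7 March 2022, so the change should be dated and documented as made before analysis.
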